## Methods

### Study Design, Participants, and Setting

This is a prospective, randomized interventional study of tablet computers (iPad 16 GB 3^rd^ generation Model A1430) as a new platform to engage older patients in actively using their PHR during and after hospitalization. We focused on tablet computers because they are light and mobile, which is helpful in the inpatient setting (eg, patients laying in gurneys for hours, patients with limited strength). The PHR used at our institution is mobile-friendly and easily accessible via Web browsers commonly used on tablets, desktops, laptops, and smartphones. We plan to enroll 100 hospitalized patients over 12 months on two general medical units at a large, academic teaching hospital (University of California, San Francisco [UCSF] Medical Center). We will also leverage EMR data to compare these 100 patients to a virtual cohort of 400 patients with the same inclusion/exclusion criteria who were already engaged in PHR use; patients in this virtual cohort will have no direct involvement in the study and will serve only as a benchmark for engagement by the 100 patients who actively participate in the study.

Each morning, research assistants will screen for new patients through UCSF’s electronic medical records by searching for medical service. While our study focus is on older patients (aged 50 years or more), we will also enroll patients younger than 50 years in order to compare and contrast patterns of use between these groups. We will include adult, English-speaking, cognitively intact patients on the medical service. To ensure patients selected will be able to use the iPad, we will exclude patients who are reported by the medical team to be cognitively impaired, blind, deaf, or involuntarily hospitalized because of mental illness. We will also exclude those who are unable to understand the study and consent to participation or who are otherwise excluded at the discretion of their medical team.

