### Randomization and Intervention

To randomize patients into intervention and control groups, we used an Internet-based coin toss random number generator (Random.org). The research assistant performs this randomization process after patient screening and consent. If the result of the coin toss is heads, the patient is enrolled in the intervention arm; if the result is tails, the patient is enrolled in the control arm. Patients were enrolled Monday through Friday only, no weekends or holidays.

Our project will provide all study participants with tablets and access codes to MyChart while they are hospitalized. Intervention patients will also receive bedside training from study research assistants on key functions of MyChart including how to view medication lists (see Multimedia Appendix 1). Through our preliminary work, we have created a semistructured tutorial for this bedside training that assistants can administer to patients. While this tutorial allows for a basic level of content uniformity for all patients, it is flexible enough to allow assistants to speed up or slow down or otherwise tailor the depth of explanation to the needs of each individual patient (see Multimedia Appendix 2). This study was approved by the UCSF Institutional Review Board and registered at Clinicaltrials.gov [NCT02109601].

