### Data Collection and Sources of Data

After creating a list of eligible patients, research assistants will approach medical teams during rounds (9:00 AM to 11:00 AM) to ensure that screened patients do not have exclusion criteria (Figure 1). The assistants will then approach patients to explain the study, including basic instructions for tablet use (on/off, opening/closing applications, and typing with touchscreen); intervention patients only will receive additional instruction in the form of the semistructured tutorial. The assistant will then leave the device with the patient and return to recollect it after about 4 to 5 hours. The assistant will perform a debrief interveiw upon return and ask patients to view and verify their preadmission medications using the medication list in their PHR. Success (gross pass/fail) in this task will be defined as patient ability to independently log in, locate their medication list, and verify their prehospitalization prescriptions (MyChart does not show inpatient medications unless they are continued at discharge). We will not require patients to correctly describe indications for every medication to receive credit; they will only be asked to identify which medications are familiar to them and which are not. We will use frequency analysis to compare the percentage of intervention group who are able to complete this task with the control group.

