### Data Analysis

Our overall objective is to assess whether inpatients can successfully use iPads for clinically useful tasks such as viewing their medications or labs or messaging their providers by using their PHR. First, we will assess this overall goal using descriptive statistics (frequency analysis) to describe time required to orient patients to tablets and basic use metrics for PHR (time spent using PHR, number of PHR tasks observed by assistant, etc). Next, we will determine the total number of log-ins to the PHR and number of clicks on different domains of the PHR (medications, labs, appointments) by querying the PHR database. We will extract basic information about whether each patient has accessed their PHR (successful log-in), when they first logged in (time from discharge), and how many times they logged in. Additionally, we will extract information about specific tasks accomplished at any point during both inpatient and postdischarge periods. We will use frequency analysis to compare the following for intervention versus control patients: rates of PHR access, time to first log-in, total number of log-ins, and number of specific tasks (refill prescription, make/change appointment, view test result, or send message to provider) accomplished within 7 days. Finally, we will assess patient satisfaction with devices overall and PHR use specifically. We will perform bivariate analyses (chi-square tests) to determine whether ability to perform key PHR tasks (eg, view medications or lab results) vary according to demographics such as age, gender, health literacy, or technology usage (eg, types of devices owned, frequency of Internet use). Although most of our findings will be descriptive, we plan to enroll 100 patients to enable detection of a 10% difference in ability to perform a key inpatient task (medication verification) and one of several key postdischarge PHR tasks (80% power, 2-sided alpha 0.05).

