### Limitations

Despite these strengths, our study has several limitations which will be important to contextualize our preliminary and final results. First, this is a relatively small study (planned enrollment of 100) which may limit our ability to detect small differences between the intervention and control groups. Second, there may be participation bias in our sample as our preliminary data suggest participants to date have been more tech-savvy than national data (ie, it may be that less tech-savvy patients are less inclined to agree to participate). Third, we did not include education or income in our survey instruments so we will not be able to determine to what extent these factors explain the tech-savviness of our participants, although we will be able to extract other traditional determinates of low technology use such as race/ethnicity and payer status (eg, Medicaid vs Medicare or private insurance) from our EMR for final analysis. Finally, we did not conduct postdischarge interviews so we do not know how patient perspectives on using their PHR might change over time; this is an important question for future studies. Future studies may also consider following patients for longer than 7 days after discharge (eg, 30 days), although we did not find any significant results at 7 days so stronger postdischarge reinforcement may be needed for future hospital-based interventions to create lasting impact.

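### One hundred patients do not give 80% power for a 10-point difference: power is about 17–25% at plausible control rates and below 80% at every control rate

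*Protocol article*

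**What the plan says.** The Study Design section sets the size: "We plan to enroll 100 hospitalized patients over 12 months on two general medical units". Randomization and Intervention allocates by a simple coin toss ("If the result of the coin toss is heads, the patient is enrolled in the intervention arm"), which gives about 50 patients per arm. Data Collection makes the inpatient endpoint binary: "Success (gross pass/fail) in this task will be defined as patient ability to independently log in, locate their medication list", plus verification of the prehospitalization prescriptions. The percentage succeeding is to be compared between the arms.

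The only justification for the size is at the end of Data Analysis: "we plan to enroll 100 patients to enable detection of a 10% difference in ability to perform a key inpatient task (medication verification", and also in "one of several key postdischarge PHR tasks (80% power, 2-sided alpha 0.05". No control-arm success rate is given. The Limitations section adds that "this is a relatively small study (planned enrollment of 100) which may limit our ability to detect small differences" between the arms, without giving a figure.

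**The concern.** Two arms of about 50 are small for a binary endpoint, and a 10-point difference between proportions in the middle of the scale usually needs several hundred patients per arm. The power statement is therefore suspect on sight.

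What is at stake is how the final result will be read. The Conclusions section says the final analysis will ask whether trained patients differ from controls, or whether tablets and log-in help alone may explain the higher engagement. If readers believe the trial had 80% power for 10 points, a non-significant comparison favours the second explanation. If power was really about 20%, the same result says little. The article already reasons this way: Limitations moves from the absence of significant findings at 7 days to the suggestion that stronger reinforcement may be needed.

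**Working it through.** **Inputs**
- Total 100 (Study Design); coin-toss allocation, so n = 50 per arm (Randomization and Intervention). Chance imbalance would only lower power.
- Binary endpoint, intervention versus control (Data Collection).
- Difference 10%, read as 10 percentage points; two-sided alpha 0.05; claimed power 80% (Data Analysis).
- Control rate p₁: not stated. Assumed range 40% to 76%, then the full range from 0% to 90%. Table 1 offers two rough guides, both pooling the arms (n = 45): 28/45 = 62% for log-in and 34/45 = 76% for reaching the medication list.
- Dropout: not stated; taken as zero, which favours the plan.

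**Formulas** (two-proportion test, pooled variance under the null), with p₂ = p₁ + d and p̄ = (p₁ + p₂)/2:
- Power ≈ Φ[(d√n − 1.96·√(2p̄(1−p̄))) / √(p₁(1−p₁) + p₂(1−p₂))]
- n per arm = [1.96·√(2p̄(1−p̄)) + 0.842·√(p₁(1−p₁) + p₂(1−p₂))]² / d²

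**Trying to reproduce the stated 80%.** With d = 0.10 and n = 50, d√n = 0.7071.
- 62% vs 72%: (0.7071 − 1.96 × 0.6650)/0.6612 = −0.90, so power is 18%.
- 76% vs 86%: (0.7071 − 1.96 × 0.5548)/0.5503 = −0.69, so power is 24.5%.

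| Control vs intervention | Power, 50 per arm | n per arm for 80% | Increase detectable with 80% power |
|---|---|---|---|
| 40% vs 50% | 17% | 388 | 27.6 points |
| 50% vs 60% | 17% | 388 | 26.7 points |
| 62% vs 72% | 18% | 346 | 24.3 points |
| 76% vs 86% | 24.5% | 241 | 19.4 points |
| 85% vs 95% | 38% | 141 | 14.7 points |
| 90% vs 100% (boundary) | 63% | 74 | – |

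Exact enumeration of the chi-square test agrees: 18% at 62% vs 72%, 25% at 76% vs 86%, 39% at 85% vs 95%. Its maximum over control rates from 0% to 90% is 75%, reached only at 0% vs 10% and 90% vs 100%. Fisher's exact test gives 38% at those extremes.

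**Other readings tried**
- 10% as a relative difference: 7% (50% vs 55%) to 15% (76% vs 83.6%).
- One-sided test: 26% to 35% for control rates of 50% to 76%, and at most 75%.
- 100 per arm instead of 100 in total: 29% to 44% for control rates of 50% to 76%.
- 100 participants against the 400-patient virtual cohort: passes 80% only at extreme rates (83% at 5% vs 15%, 88% at 85% vs 95%). That cohort is identified from records alone and cannot perform a task observed by an assistant.
- One-sample test: needs 108 patients at 80% vs 90% and 79 at 85% vs 95%, but the design compares two arms.

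**Precision.** The 95% half-width for the arm difference is 1.96·√[(p₁(1−p₁) + p₂(1−p₂))/50].
- Equal rates in both arms: 19.0 points at 62% and 16.7 points at 76%.
- True 10-point difference: 18.3 points at 62% vs 72% and 15.3 points at 76% vs 86%.

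**The case against.** The best case on the other side accepts the arithmetic and disputes its reach.

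- **Unstated control rate.** The 17–25% range is conditional, and the fuller protocol appendix is not at hand. Table 1 also shows 82% to 85% for other functions; at 85% power is 38% and the detectable increase about 15 points. This stands as a condition on the range, but no control rate reaches 80%.
- **Proxy rates.** The 62% and 76% pool both arms and are components of the success definition. If training works, the control rate lies below the pooled rate, and a composite that requires independent log-in may not exceed the log-in rate. This also stands, but it points towards the less favourable end of the range.
- **Postdischarge tasks.** No rate for these is given, so no specific power can be quoted. The ceiling still applies to any single pass/fail task compared between arms of 50.
- **The article's own caveats.** It calls most findings descriptive and admits the study is small. That deserves credit, but the descriptive remark introduces the power claim as an exception. The limitation neither gives a size nor withdraws the 80%, so beside a claimed 10% a reader would take small differences to mean those below 10 points.
- **Severity.** The remedy is wording in a small study that is already enrolling. That limits the cost of the correction; it does not make the stated figure right.

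**Conclusion.** The power statement is wrong as written. With 100 patients in two arms of about 50, no control rate gives 80% two-sided power for a 10-point difference; the best attainable is 75%, at the boundary. For control rates of about 40% to 76%, power is 17% to 25% and the increase detectable with 80% power is about 28 down to 19 points. A true 10-point effect would then be missed 75% to 83% of the time. Reaching the stated power near the preliminary rates would take 482 patients (2 × 241, control 76%) to 692 (2 × 346, control 62%).

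The verdict rests on equal arms, no missing data and a 10-point absolute reading. Relaxing the first two, or taking the 10% as relative to the control rate, lowers power further. Only the quoted ranges depend on the assumed control rate.

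**What to change.** Keep 100 patients and replace the power sentence in Data Analysis with one that names its assumption, for example:

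> With about 50 patients per arm and a two-sided alpha of 0.05, the study has 80% power to detect an increase in medication-verification success of about 19 points if the control rate is 76%, 24 points if it is 62%, and 27 to 28 points if it is 40% to 50%. Power for a 10-point increase is about 17% to 25% over this range.

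Remove the matching 80% claim for the postdischarge tasks, or restate it with an assumed rate for the named task. Report the arm difference with its 95% confidence interval; the expected half-width is about 17 to 19 points if both arms share a rate of 62% to 76%, and about 15 to 18 points if the true difference is 10 points from those rates. In Limitations, put these figures beside the existing caveat and state that a non-significant result does not exclude a 10-point effect.

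The cost is wording only: no extra patients and no change to endpoint or analysis. The stated power becomes less favourable, but correct.

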## Results

Preliminary data from our protocol are show in Table 1. To date, we have enrolled 45 patients; approximately half our sample comprises older adults (50-79 years, 22) and about half (24) are female. Most participants reported owning a laptop computer (34, 75%) or smartphone (29, 64%); desktop and tablet computer ownership were lower at 54% (24) and 51% (23), respectively. A strong majority of patients (39, 86%) indicated they access the Internet daily. While 82% (37) reported looking up health information for themselves on the Internet in the past 12 months, only slightly more than half (27, 59%) had used the Internet to communicate with a health care provider and few had used it to schedule a medical appointment (18, 40%) or refill a prescription (17, 37%).

**Table 1 table1:** Participant characteristics (n=45).

		n (%)
Age (years)	
	18-39	9 (19)
	30-49	14 (32)
	50-79	22 (49)
Gender	
	Female	24 (53)
	Male	19 (42)
	Declined/no response	2 (4)
Device ownership	
	Desktop computer	24 (54)
	Laptop computer	34 (75)
	Smartphone	29 (64)
	Tablet computer	23 (51)
Internet use	
	Daily	39 (86)
	Several times a week	3 (6)
	Once a week or less	1 (3)
Prestudy online health tasks	
	Looked up health information	37 (82)
	Communicated with provider	27 (59)
	Scheduled medical appointment	18 (40)
	Refilled prescription	17 (37)
Orientation to iPad	
	Required 15 minutes or less	36 (81)
	Required 16 to 30 minutes	4 (9)
	Required 30 minutes or more	5 (10)
Independently access/navigate PHR on iPad	
	Log in/verify info	28 (62)
	Medications list page	34 (76)
	Medications refills page	18 (40)
	Scheduled appointments page	38 (85)
	Test results page	38 (85)
	Secure messaging page	37 (82)

Among older adults, 70% (15) owned a laptop, 58% (13) owned a desktop computer, 52% (11) owned a smartphone, and 42% (9) owned a tablet. Thus, mobile technologies pose an excellent venue to interact with this patient population. Trained research assistants spent at least 30 minutes with those patients who needed more assistance to become familiar with the tablets, but the majority needed 15 minutes or less, suggesting that most of them felt comfortable with using this technology. Indeed, our findings to date suggest that inpatients of all ages in both intervention and control groups require only minimal orientation from research assistants to use basic (eg, access Internet, check email) as well as more advanced functions (watch videos, complete tasks requiring more advanced navigation): 90% (41) of patients required 30 minutes or less for device orientation and 81% (36) required 15 minutes or less. Additionally, we found that after focused bedside teaching, most patients in our study were able to perform one or more key function in their PHR. These key functions included viewing their medication list (34, 76%), viewing scheduled appointments (38, 85%), viewing test results (38, 85%), and sending a secure message to their primary care provider (37, 82%). Additionally, 75% (34) reported they were satisfied or very satisfied with iPad tablet use for bedside access to their PHR to accomplish these tasks.

Because data is still being collected to compare patient groups within our study (intervention vs control), we compared PHR use among all participants (to date) in both groups to a virtual cohort of patients identified as regular users of their PHR prior to hospitalization. In most areas, both groups were similar, but our study group had significantly higher activity in medication list views (mean 2.12 views vs 1.07) and the virtual cohort had significantly higher use of the provider messaging function (mean 4.34 views vs 1.63) (Table 2).

**Table 2 table2:** Patient characteristics and PHR use in study participants compared to a virtual cohort of regular PHR users.

		Study group (n=45)	Virtual cohort (n=400)	*P* value
Inpatient characteristics				
	Hospital length of stay, days	5.79	4.51	.37
	Previous PHR experience, n (%)	22 (50)	400 (100)	<.01
PHR use during hospitalization				
	Logins per person, mean	2.74	2.99	.64
	Medication tab views, mean	2.12	1.07	<.01
	Test results tab views, mean	1.42	2.21	.28
	Appointments tab views, mean	0.69	1.34	.11
	Provider messaging inbox views, mean	1.63	4.34	.04
PHR use after hospitalization (up to 7 days after discharge)				
	Logins per person, mean	4.04	3.87	.83
	Medication tab views, mean	2.93	1.46	<.01
	Test results tab views, mean	6.28	4.29	.37
	Appointments tab views, mean	2.72	2.01	.32
	Provider messaging inbox views, mean	3.91	6.11	.36

**Table 3 table3:** Adjusted PHR use during hospitalization by study group compared to virtual cohort group.

	Multivariable logistic regression^a^	
	OR for study group vs virtual cohort group mean	95% CI
Medication tab views	2.4	1.5-4.2
Test results tab views	1.1	0.7^-^1.8
Appointments tab views	0.71	0.5^-^1.1
Provider messaging inbox views	0.70	0.5^-^1.1

^a^Adjusted for age, gender, race/ethnicity, length of stay, and prior PHR experience.

In analyses adjusted for confounding, the higher rate of provider messaging seen in Table 3 disappeared with adjustment; however, the higher rate of medication list views persisted (odds ratio [OR] 2.4) (Table 3). In adjusted analyses of PHR use after discharge, there were no significant differences between the virtual cohort and the study group.

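### Table 3's confidence intervals are too narrow for its stated binary logistic model with 45 and 400 patients, and the change from mean views to odds ratios leaves the claimed effect of adjustment unsupported

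*Protocol article*

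**What the plan says.** Table 2 (Results) compares 45 study patients, both arms pooled, with a virtual cohort of 400 on mean log-ins and mean tab views per person. For use in hospital, the accompanying text reports more medication list views in the study group (2.12 vs 1.07) and, for messaging, that "the virtual cohort had significantly higher use of the provider messaging function (mean 4.34 views vs 1.63".

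Table 3 gives adjusted results for use in hospital. Its heading is "Multivariable logistic regression^a", its effect column is "OR for study group vs virtual cohort group mean", and its footnote reads "Adjusted for age, gender, race/ethnicity, length of stay, and prior PHR experience". The rows, with 95% CIs, are:

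- medication views: 2.4 (1.5 to 4.2)
- test results views: 1.1 (0.7 to 1.8)
- appointments views: 0.71 (0.5 to 1.1)
- messaging inbox views: 0.70 (0.5 to 1.1)

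The text then concludes that "the higher rate of provider messaging seen in Table 3 disappeared with adjustment; however, the higher rate of medication list views persisted". The Discussion (Principal Findings) relies on the medication result to suggest that tablets with basic help may raise inpatient engagement. It also says that each arm will later be compared separately with the cohort.

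**The concern.** A logistic regression with 45 patients in one group can give only limited precision, whatever the data look like. The Table 3 intervals look tighter than that limit. If so, the uncertainty around the article's only adjusted positive result is not what the stated model would give.

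There is a second, independent difficulty. The unadjusted comparison is in mean counts and the adjusted one is in odds ratios. The event behind the odds is not defined (any view, views above some cut-point, or something else), and no unadjusted odds ratio is shown. A reader cannot tell whether an estimate moved because of the covariates or because the outcome changed.

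**Working it through.** **Inputs.** Group sizes 45 and 400, and prior PHR experience in 22 study patients and all 400 cohort patients (Table 2). Odds ratios, 95% CIs and covariates (Table 3 and its footnote). z = 1.96.

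**Floor for a binary logistic model, one record per patient.** Each patient carries weight p(1 − p), which is at most 1/4. Hence

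SE(log OR) ≥ √(4/45 + 4/400) = √(0.0889 + 0.0100) = 0.314.

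The smallest possible ratio of upper to lower limit is exp(2 × 1.96 × 0.3145) = 3.43. Covariates can only remove information about the group term, so the floor also holds after adjustment. A search over event counts with profile-likelihood intervals gave a minimum ratio of 3.46, so the interval method does not explain the gap.

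**Printed intervals against the floor.** The rounding column moves each limit outwards by 0.05.

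| Row | Printed ratio | Largest ratio with rounding | Floor |
|---|---|---|---|
| Medication | 4.2/1.5 = 2.80 | 4.25/1.45 = 2.93 | 3.43 |
| Test results | 1.8/0.7 = 2.57 | 1.85/0.65 = 2.85 | 3.43 |
| Appointments | 1.1/0.5 = 2.20 | 1.15/0.45 = 2.56 | 3.43 |
| Messaging | 1.1/0.5 = 2.20 | 1.15/0.45 = 2.56 | 3.43 |

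The printed table is not reproduced in any row. The implied SE is ln(ratio)/(2 × 1.96), and the study patients needed in the best case are 4/(SE² − 4/400):

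- Limits 0.5 to 1.1: SE 0.201, about 131 patients (about 85 with rounding in the table's favour).
- Medication limits: SE 0.263, about 68 patients (about 61 with rounding).

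**Other readings tried.**

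- *Ordinal (proportional-odds) logistic with many categories.* SE ≈ √(3 × (1/45 + 1/400)) = 0.272, ratio about 2.91 (2.94 when computed at an odds ratio of 2.4). This is at the rounding limit of the medication row (2.93) and above that of the other three.
- *90% intervals.* The floor is 2.81, which could fit the medication and test results rows but not the other two.

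**Narrowest intervals at the printed odds ratios, SE 0.3145.** The multiplier is exp(1.96 × 0.3145) = 1.852.

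- Medication: 2.4/1.852 to 2.4 × 1.852 = 1.30 to 4.45.
- Messaging: 0.70/1.852 to 0.70 × 1.852 = 0.38 to 1.30.

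**If prior PHR experience entered as the yes/no variable of Table 2.** Every cohort patient is a prior user, so only the 22 prior users in the study group have cohort counterparts. Then SE ≥ √(4/22 + 4/400) = 0.438, the floor ratio is 5.57, and the narrowest medication interval is 1.02 to 5.66. The other covariates could only widen it.

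**Change of scale.**

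| In-hospital outcome | Ratio of means, Table 2 | Adjusted OR, Table 3 |
|---|---|---|
| Medication | 2.12/1.07 = 1.98 | 2.4 |
| Test results | 1.42/2.21 = 0.64 | 1.1 |
| Appointments | 0.69/1.34 = 0.51 | 0.71 |
| Messaging | 1.63/4.34 = 0.38 | 0.70 |

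The two columns measure different things, so the shift between them mixes adjustment with the change of outcome.

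**The case against.** Several stronger conclusions are tempting, and the document does not support them.

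- *No logistic model of any kind could give these intervals.* The bound is exact for a binary outcome only. An ordinal model comes within rounding for the medication row, which is the row that matters most.
- *Views or sessions were analysed as if independent.* The article never says so. A mislabelled count model is another possibility, since the column header mentions a mean. A patient-level negative binomial with dispersion of about 2.3 would give the medication width, although appointments would need only about 0.3. The cause stays open.
- *The medication result is wrong.* It still excludes 1 at the floor, and just does so with 22 informative patients. That second figure also assumes yes/no coding of prior experience, which the footnote does not state.
- *The messaging difference is really significant.* A wider interval still includes 1, so non-significance after adjustment stands.
- *The final analysis will repeat the error.* The Data Analysis section names frequency analysis and chi-square tests, and nothing says that the Table 3 model will be reused.

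It is also fair to say that the comparison is an interim look at 45 of 100 planned patients against a non-randomised benchmark, which the article calls preliminary. It touches neither the randomisation nor the comparison of intervention with control. That lowers the severity. It does not answer the mismatch, because the figures are printed and the article's own group sizes rule them out under the model named.

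**Conclusion.** The point holds. A binary logistic model with one record per patient cannot give any of the four printed intervals: the floor ratio is 3.43, and the printed ratios reach at most 2.93, 2.85, 2.56 and 2.56. This rests only on the group sizes, the 95% level and the model label. Label, sample size and intervals cannot all be right, and the article does not show which one is wrong.

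The claim that the medication difference persisted is not overturned, but its printed precision cannot be relied on, and the result may prove borderline. The claim that the messaging difference disappeared with adjustment does not follow. The scale changed at the same step, and an interval at least as wide as 0.38 to 1.30 remains compatible with a large difference. The sentence also cites Table 3 for an unadjusted difference that stands in Table 2.

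Severity is moderate: the comparison is preliminary and non-randomised, and the intervention-control comparison is unaffected.

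**What to change.** 1. State the event modelled and the unit of analysis for Table 3, and how prior PHR experience was coded.
2. Refit with one record per patient. A count model with robust standard errors is one suitable choice. Length of stay should enter once, as a covariate or as an offset.
3. Print unadjusted and adjusted estimates with 95% CIs side by side on the same scale, and replace the Table 3 intervals.
4. Reword the sentence on the messaging difference to match, ascribing a change to confounding only if the estimate moves on that one scale. Cite Table 2 for the unadjusted difference.
5. If adjusted arm-versus-cohort comparisons are made in the final analysis, use the corrected patient-level model. With about 50 patients per arm the binary logistic floor would be √(4/50 + 4/400) = 0.30, a ratio of exp(3.92 × 0.30) = 3.24, which is a quick check on the output.

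A count model does not supply cohort counterparts for study patients without prior PHR experience, so that limit should be stated beside the result.

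The cost is a rerun on data already held. The intervals will probably widen, and the medication result may become borderline.
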